##### 2.5.2.2 Menopause-specific quality of life scale

MENQOL is used to evaluate life quality of peri-menopausal women. It contains 27 questions related to vasomotor symptoms, psychological symptoms, physiological symptoms, and sexual life. A lower MENQOL score indicates PMPS has a less influence on life quality. It will be measured at baseline and 12, 16 weeks after randomization.

##### 2.5.2.3 Hamilton depression scale

HAMD will be used to evaluate the depressive condition of PMPS in this trial. Most of the items are scored on a 5-level scale with 0–4 points, a few items is a 3-level scale with 0–2 points. A higher score indicates the more severe depression. In this study, it will be evaluated at baseline and 12, 16 weeks after randomization.

##### 2.5.2.4 Hamilton anxiety scale

HAMA contains 14 items related to a number of anxiety symptoms. Each of items is scored on a 5-level scale with 0–4 points. A higher score indicates the more severe anxiety. In this study, it will be evaluated at baseline and 12, 16 weeks after randomization.

### 2.6 Mechanism outcomes

1) Sex hormone: the levels of E2, FSH and luteinizing hormone (LH) in serum are detected using ELISA.2) Monoamine neurotransmitter: serum serotonin (5-HT), norepinephrine (NE) and dopamine (DA) levels were detected using ELISA.3) Vascular vasomotor factor: serum nitric oxide (NO), calcitonin gene-related peptide (CGRP) and endothelin-1 (ET-1) levels were detected using ELISA.4) Expression of serum protein and mRNA level of phosphatidylinositol 3-active enzyme (PI3K), protein activator enzyme B (Akt) and phosphorylated protein kinase B (pAkt) were detected using Western blot and polymerase chain reaction (PCR). These outcomes are measured before and after treatment.

### 2.7 Safety outcomes

In order to exclude serious heart, liver, and kidney diseases, all participants will also receive urine, stool, blood routine, liver function (ALT, AST), kidney function (BUN, creatinine) and ECG examination before and after treatment. Participants will inform the researchers adverse events or uncomfortable symptoms by WeChat software, telephone, or short message. Adverse events should be recorded in the Case Report Form and resolved immediately. Serious adverse events should be reported immediately to the principal investigator. The details of outcome assessment chart is given in Table 1.

**TABLE 1 T1:** Trial processes chart.

Period	Enrollment	Baseline	Treatment			Follow-up
Time points	Week -1	Week 0	Week 4	Week 8	Week 12	Week 16
Patients						
Medical history	√					
Physical examination	√				√	
Laboratory examination	√				√	
Informed consent	√					
Randomization	√					
Intervention						
HongHua XiaoYao Pills (HHXYP) group			0.39g/pill, 2 pills, three times daily			
Oryzanol Control (OC) group			10mg/pill, 2 pills, three times daily			
Outcomes						
the modified Kupperman Index (KI)	√	√	√	√	√	√
Hot flash scale (HFs)	√	√	√	√	√	√
MENQOL		√			√	√
HAMD		√			√	√
HAMA		√			√	√
Serum E2, FSH and LH levels		√			√	
Serum NE, 5-HT and DA levels		√			√	
Serum NO, ET-1 and CGRP levels		√			√	
Expression of PI3K, Akt, and pAkt		√			√	
Trial evaluation						
Safety of medicine			√	√	√	√
Adverse event			√	√	√	√
Reasons of drop-outs or withdrawals			√	√	√	
Patient’s compliance					√	

E2, estradiol; FSH, follicle-stimulating hormone; LH, luteinizing hormone; NO, nitric oxide; ET-1, endothelin-1; CGRP, calcitonin gene-related peptide; NE, norepinephrine; 5-HT, serotonin; DA, dopamine; PI3K, phosphatidylinositol 3-active enzyme; Akt, protein activator enzyme B; pAkt, phosphorylated protein kinase B.

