## Abstract

**Background:** Peri-menopausal syndrome (PMPS) has a high incidence rate and seriously affects the physical and mental health of women. Honghua Xiaoyao Pill (HHXYP) is a Chinese patent medicine, which has been reported to be used to treat PMPS. However, there is still a lack of randomized clinical trial to evaluate the efficacy and safety of HHXYP on life quality, mood and vasomotor symptoms for PMPS women. This study aims to investigate whether HHXYP is effective and safe in treating PMPS and the possible mechanism.

**Methods:** A multicenter, randomized, controlled clinical trial will be conducted in China to evaluate the efficacy and safety of HHXYP. Sixty women with peri-menopausal syndrome will be recruited at three centers and randomly in a 1:1 ratio to a treatment group using HHXYP (HHXYP group) and a control group using oryzanol (OC group). Participants will be treated with HHXYP or oryzanol for 12 weeks and followed up for 4 weeks. The primary outcome is the modified Kupperman Index (KI), which will be measured at baseline and 4, 8, 12, 16 weeks after randomization. The secondary outcomes include Hot flash scale (HFs), Menopause-Specific Quality of Life Scale (MENQOL) and Hamilton Depression/Anxiety Scale (HAMD/HAMA). The HFs are measured at the same point as the KI, other secondary outcomes are measured at baseline and 12, 16 weeks after randomization. The other outcomes are the levels of serum sex hormone, monoamine neurotransmitter, vascular vasomotor factor and the expression of phosphatidylinositol 3-active enzyme (PI3K)/protein activator enzyme B (Akt), which will be measured at baseline and 12 weeks after randomization. Adverse events will also be reported.

**Discussion:** HHXYP is a potential alternative Chinese patent medicine for PMPS. This trial will provide evidence for HHXYP on improving the quality of life, mood and vasomotor symptoms, and sex hormone levels of PMPS patients.

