## 1 Introduction

Peri-menopause is defined as a period from 2 to 8 years before menopause and 1 year after final menstruation (Speroff, 2002). Nearly all women will experience this period, which is characterized by disturbing symptoms including hot flashes, night sweats, fatigue, insomnia, vaginal dryness and sexual dysfunction, clinically called “peri-menopausal syndrome”. These symptoms results from ovarian dysfunction, which leads to estrogen level fluctuations or reduction, hypothalamic-pituitary-ovarian axis dysfunction, and imbalance of neurotransmitters or hormones. Hot flashes and night sweats are the most frequently reported symptoms, which called as vasomotor symptoms (VMS). In addition, there is evidence to suggest that women during this reproductive transition were more likely to suffer from peri-menopause depression (PMD), leading to a reduced quality of life and increased burden for healthcare needs (Maki et al., 2019).

The conventional treatment for PMPS is hormone replacement therapy (HRT), but many patients refuse to long-term use this treatment because their concern for side-effects such as increased risks of endometrial and breast cancer, stroke, glucose intolerance and thromboembolic disease (Shapiro et al., 2013; Wassertheil-Smoller et al., 2003; Lumsden, 2016; Flores et al., 2021). Standard antidepressants have also been studied as a treatment for both the mood and vasomotor symptoms in peri-menopausal women, but many women are reluctant to use these because of their adverse effect such as weight gain, fatigue and drowsiness (Maki et al., 2018; Maki et al., 2019). Traditional Chinese medicine (TCM) has been widely used for more than 2,000 years to treat PMPS, especially the mood and vasomotor symptoms, with clinical therapeutic effects, safety and low cost.

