#### 2.3.2 Inclusion criteria

Participants are deemed peri-menopause according to STRAW classification (Harlow et al., 2012) and meet the following criteria:1) Health women aged 45–60 years;2) Menstrual disturbance (prolonged menstrual cycle or oligomenorrhea) lasting over 3 months, or amenorrhea for 2–12 months;3) Suffering from vasomotor symptoms (hot flashes, sweating), somatic symptoms (insomnia, fatigue, headache, paresthesia), psychological symptoms (nervousness, melancholia), or urogenital symptoms (dyspareunia, vaginal dryness, urinary infection);4) Serum follicle-stimulating hormone (FSH) > 10 IU/L, or decline of estradiol (E2);5) Peri-menopausal symptoms have not been treated with HRT or other drugs in the last 2 months;6) Uterus and bilateral accessories are complete and without resection;7) Conscious and patients accepted informed consent.

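### Single E2, FSH and LH draws at Weeks 0 and 12 in women of mixed menstrual status, compared without a term for that status, lose precision on a mechanism outcome

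*Protocol article*

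**What the plan says.** Protocol article, section 2.7, Table 1: the row "Serum E2, FSH and LH levels" is ticked at Week 0 and Week 12 only. The Abstract gives the same timing for the hormones and the other markers, "which will be measured at baseline and 12 weeks after randomization", and section 2.6 says "These outcomes are measured before and after treatment". None of these places ties the draw to a day of the cycle.

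Section 2.3.2, criterion 2, defines the menstrual status of eligible women: "Menstrual disturbance (prolonged menstrual cycle or oligomenorrhea) lasting over 3 months, or amenorrhea for 2–12 months". Criterion 6 adds "Uterus and bilateral accessories are complete and without resection". Some participants can therefore still be cycling, while others have not bled for months.

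The Introduction describes ovarian dysfunction, "which leads to estrogen level fluctuations or reduction", as the origin of the syndrome. The Abstract expects the trial to give evidence on "vasomotor symptoms, and sex hormone levels of PMPS patients".

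Section 2.8 compares continuous variables between groups by variance analysis and names no term for menstrual status. Section 2.2 describes 1:1 randomisation and mentions no stratification by menstrual status.

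**The concern.** In a woman with long or irregular cycles, two samples 84 days apart (12 × 7) have no fixed relation in cycle phase. Her change in E2, FSH or LH then contains a phase difference as well as any treatment response. In a woman with long amenorrhea this component should be smaller. When both kinds of women are pooled in one variance analysis, the differences between them and the phase noise all go into the error term.

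At stake is whether about 30 women per arm can show a hormone effect if one exists. The article itself treats fluctuating estrogen as part of the condition and lists sex hormones among the things the trial will inform, so the loss of precision deserves attention. The primary outcome, the modified Kupperman Index, is not touched.

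**Working it through.** **1. Does random phase bias the comparison between arms?** A null simulation used 30 women per arm and 20,000 runs. Residual SD was 1, and each draw received a random phase shift of 0 or 3. One shift has variance (3/2)² = 2.25, so the difference of two independent shifts has variance 4.5, which is 4.5 times the residual variance. The two-sample t-test rejected in 0.051 of runs at nominal 0.05. Phase noise that is random in both arms leaves the type I error intact, so the harm is lost precision. A before–after reading within one arm, without the concurrent control, would be more exposed.

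**2. The plan's own figure.** The article gives no effect, SD or power for any hormone. Its only calculation (section 2.3.4) is for the Kupperman Index: changes of 9 ± 7 and 3 ± 7, so d = (9 − 3)/7 = 0.857, with 30 per group. Two-sided noncentral-t power at that size is 0.904. (This matches β = 0.10. The printed β = 0.01 would need 51 per group, which is a separate matter.) The 0.857 is borrowed below only as a benchmark and is not a hormone effect. At 30 per group the smallest effect detectable with 80% power is d = 0.74, before any cycle noise.

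**3. Power as the noise share grows.** Let f be the share of hormone variance due to phase and fluctuation (assumed), and d the effect without that noise. The effective effect is d√(1 − f). At d = 0.857 and f = 0.5 it is 0.857 × 0.707 = 0.606.

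| d | f = 0 | f = 0.25 | f = 0.50 | f = 0.75 | f = 0.90 |
|---|---|---|---|---|---|
| 0.5 | 0.48 | 0.38 | 0.27 | 0.16 | 0.09 |
| 0.857 | 0.90 | 0.81 | 0.64 | 0.37 | 0.18 |
| 1.0 | 0.97 | 0.91 | 0.77 | 0.48 | 0.23 |

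**4. Only some women contribute the noise.** Let p be the share still cycling and k the added phase variance in those women, relative to the remaining variance. Both are assumed. The average variance becomes 1 + pk, the standard error rises by √(1 + pk), the effective sample is 1/(1 + pk), and f = pk/(1 + pk).

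| p | k = 1 | k = 2 | k = 4 |
|---|---|---|---|
| 0.25 | ×1.12, 80% | ×1.22, 67% | ×1.41, 50% |
| 0.50 | ×1.22, 67% | ×1.41, 50% | ×1.73, 33% |
| 1.00 | ×1.41, 50% | ×1.73, 33% | ×2.24, 20% |

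Each cell shows the standard-error factor and the effective sample. For example, p = 0.50 and k = 2 gives 1 + 1 = 2, so √2 = 1.41 and f = 0.5, which is the f = 0.50 column in step 3.

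**5. What a menstrual-status factor can recover.** It removes the part of the error that comes from differing mean levels in cycling and amenorrheic women. It does not remove phase noise among the cycling women. With all 60 women the error degrees of freedom go from 2 × 30 − 2 = 58 to 57.

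**The case against.** The strongest case against is that the article lists visit weeks without sampling conditions for any assessment, and a cycle-day rule for a blood draw is the kind of detail a condensed article leaves to the full protocol or a laboratory manual. This stands in part: the text does not show that draws will be taken in disregard of the cycle, and a reader should not infer that. What remains is that the article itself states the timing, the mixed eligibility and the form of analysis, and that the stated analysis can be improved. If the full documents already hold a cycle rule or a status factor, citing it closes the point.

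Two stronger readings are tempting. One is that an imbalance in phase or in the share of amenorrheic women could pass for a drug effect. The documents do not support this: chance imbalance is ordinary sampling error, already covered by the significance level, as step 1 shows. The other is that the hormone comparison is likely to be uninformative. That needs a hormone variance and the share of cycling women, and the article gives neither.

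It is also fair that E2, FSH and LH are mechanism outcomes, so noise in them cannot change the primary conclusion.

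Finally, tying each draw to the nearest bleed would bring its own problems. In women with infrequent periods that bleed may be weeks away. The baseline sample could then fall after treatment starts or before consent, and the second after treatment ends. Moving only these hormones would need a separate blood draw, because Table 1 takes the neurotransmitters, vasomotor factors and PI3K/Akt markers at the same visits. These objections stand, and the fix is limited accordingly.

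**Conclusion.** The point holds as a modest loss of precision that can be partly avoided. Fixed-week single draws, eligibility that mixes cycling and amenorrheic women, and a variance analysis that names no status term together put noise into the E2, FSH and LH comparison. The randomised comparison stays unbiased, and only a mechanism outcome is affected.

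The size cannot be fixed from the document. The tables above rest on assumed f, p and k and on a benchmark effect taken from the Kupperman calculation. They show that the loss can range from small (effective sample 80%) to large (20%), not where this trial lies. The conclusion also assumes that the full protocol holds no cycle rule or status adjustment beyond what the article states.

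**What to change.** Keep the hormone draws at the existing Week 0 and Week 12 visits. Add one CRF field at each draw for days since the last menstrual period. Analyse Week 12 E2, FSH and LH with baseline menstrual status (cycling or amenorrheic) as a factor in the variance analysis. That status is already established when criterion 2 is checked.

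Optionally, where a woman is still bleeding, schedule the whole Week 0 and Week 12 blood draw, not just the sex hormones, in an early-cycle window. Do this only if the first draw stays before the first dose and the second within the treatment period; otherwise sample at the visit.

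Cost: one CRF field, one degree of freedom, and some scheduling effort if the window is used. The factor and the CRF field need no extra sample. Section 2.10 reports nine women enrolled by 1 June 2022, so at that date up to 51 of the planned 60 could still have had the field recorded from baseline. For those already enrolled, status at entry should be recoverable from the eligibility record.

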### 2.8 Statistical analysis

All data will be statistically analyzed using SPSS 20.0 software by a special analysts who is blinded to this trial. Continuous variables with normal distribution are presented as mean ± standard deviation (SD), and categorical variables are presented as frequency/percentage. All of the analyses will be performed on intention-to-treat (ITT) principle. Pearson’s chi-squared test or Fisher’s exact test are used to compare the frequency of categorical variables. Non-parametric Mann-Whitney test or Kruskal–Wallis test is used to compare data sets involving non-normal distribution. The comparison of continuous variables between groups will be evaluated by variance analysis. The main outcome scales at different time points will be analyzed by repeated measurement analysis of variance (ANOVA). Significance level is set as *p*-value less than 0.05.

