## 2 Materials and methods

### 2.1 Study design

This is a multicenter, randomized, controlled trial to investigate the efficacy and safety of HHXYP by comparing with oryzanol. Sixty participants will be included from the following three hospitals: Tongji hospital, Tongji Medical College, Huazhong University of Science and Technology (HUST); Maternal and Child Hospital of Hubei Province, Tongji Medical College, HUST; Wuhan Maternal and Child Health Hospital, Tongji Medical College, HUST. Tongji Hospital is the central structure of the study.

The duration of this study is 17 weeks including screening period of 1 week, treatment period of 12 weeks, and follow-up period of 4 weeks. Informed consent form signed by all qualified participants before enrollment. The Ethics Committee of Tongji Medical College, Huazhong University of Science and Technology approved this trial (approval number:2021S188). The protocol design conformed to the Declaration of Helsinki (Version Edinburgh 2000) and registered on the Chinese Clinical Trial Registry (ChiCTR2100050783). The flow chart of the study has been presented in Figure 1.

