### 2.2 Randomization, allocation concealment and blinding

These participants will be randomly in a 1:1 ratio to HHXYP treatment group and OC group. An independent statistician will use SPSS software to generate the randomization sequence. The designated researcher in the central structure will prepare the assignments in opaque envelopes in sequence, and inform the researcher of the matching card number either by text message or *via* mobile communication application. To ensure blindness in this trial, both of HHXYP and oryzanol pills were packaged with the same appearance throughout the study process, outcome assessors and the data analysts will be blinded to the group allocation.

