#### 2.3.4 Sample sizes

According to a previous study of peri-menopausal women in China (Zhang et al., 2014), we assumed that the mean ± standard deviation (SD) differences in the change in total KI score of the intervention group and the control group were 9 ± 7 and 3 ± 7. PASS 15 software was used for sample size calculation. We determined a sample size of 30 women for each group, with α equal to 0.05 (two-sided) and β equal to 0.01.

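### No baseline covariate is named for any between-group comparison, which gives up precision with 30 women per arm

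*Protocol article*

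**What the plan says.** Section 2.8 gives three rules for continuous data.

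- The general rule: "The comparison of continuous variables between groups will be evaluated by variance analysis".
- The alternative: "Non-parametric Mann-Whitney test or Kruskal–Wallis test is used to compare data sets involving non-normal distribution".
- For the main scales followed over several visits, repeated-measures ANOVA. The text does not say whether baseline is one of the visits, or whether the test is the group effect or the group-by-time interaction.

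None of the three names a covariate.

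Baseline values are nevertheless collected throughout. KI and hot flashes are recorded at baseline and weeks 4, 8, 12 and 16 (sections 2.5.1 and 2.5.2.1). Of MENQOL, section 2.5.2.2 says "It will be measured at baseline and 12, 16 weeks after randomization", and HAMD and HAMA follow the same schedule. Of the serum markers, section 2.6 says "These outcomes are measured before and after treatment", which Table 1 places at weeks 0 and 12.

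The sample size in section 2.3.4 is built on change in KI. Section 2.8 does not say whether change or raw scores are compared.

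**The concern.** When an outcome has a baseline value that correlates with follow-up, an analysis of the post-treatment value alone leaves explainable variation in the error term. A change score removes some of it but generally over-corrects. Regression on baseline uses the information at its best weight. In a trial of 60 women, that difference in variance can be worth several women per arm.

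The mechanism markers are the plainest case. They are not scales and have one post-baseline value, so they fall under the general rule or the rank-test rule, and neither sentence uses baseline. A Mann-Whitney test also yields no baseline-adjusted estimate of effect.

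For KI the problem is different. The repeated-measures sentence leaves the tested term and the role of baseline open, and the power of the primary analysis depends heavily on both.

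**Working it through.** **Inputs from the protocol article**

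- Section 2.3.4: "differences in the change in total KI score of the intervention group and the control group were 9 ± 7 and 3 ± 7", taken as a difference of 9 − 3 = 6 with a change-score SD of 7 in each group.
- Section 2.3.4: "We determined a sample size of 30 women for each group, with α equal to 0.05 (two-sided) and β equal to 0.01".
- Section 2.2: 1:1 allocation. Section 2.1: sixty participants, so 30 per arm.

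**Assumption.** The baseline to follow-up correlation ρ is not in the document. A range of 0.3 to 0.7 is used, with equal variance at both times.

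**The plan's own figure.** n per group = 2(SD/difference)²(z for α + z for power)².

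- At β = 0.01: 2 × (7/6)² × (1.960 + 2.326)² ≈ 50.01, so 51 per group and not 30.
- At β = 0.10: 2 × (7/6)² × (1.960 + 1.282)² ≈ 28.6, so 29 (30 with the t distribution).
- Power at 30 per group by the noncentral t is 90.4%.

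The mismatch with the printed β is a separate matter. Here, 90.4% is the reference power for an unadjusted change score.

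**Variance ratios.** With raw variance σ², the error variance is σ² for the post score, 2σ²(1 − ρ) for change and σ²(1 − ρ²) for ANCOVA. Hence ANCOVA/post = 1 − ρ² and ANCOVA/change = (1 + ρ)/2.

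**KI power.** A change SD of 7 implies post SD = 7/√(2(1 − ρ)) and ANCOVA residual SD = 7√((1 + ρ)/2). Difference 6, 30 per arm, two-sided 0.05:

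| | ρ = 0.3 | ρ = 0.5 | ρ = 0.7 |
|---|---|---|---|
| ANCOVA/post variance | 0.91 | 0.75 | 0.51 |
| ANCOVA/change variance | 0.65 | 0.75 | 0.85 |
| Post SD | 5.92 | 7.00 | 9.04 |
| ANCOVA residual SD | 5.64 | 6.06 | 6.45 |
| Power, ANCOVA | 98.2% | 96.5% | 94.3% |
| Power, change score | 90.4% | 90.4% | 90.4% |
| Power, post score | 97.1% | 90.4% | 71.5% |

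**Repeated-measures ANOVA for KI.** Simulated with 4,000 runs, compound symmetry and assumed group differences of 0, 2, 4, 6 and 6 at weeks 0, 4, 8, 12 and 16:

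| | ρ = 0.3 | ρ = 0.5 | ρ = 0.7 |
|---|---|---|---|
| Group by time, baseline as a visit | 92% | 92% | 92% |
| Group main effect, baseline as a visit | 94% | 71% | 43% |
| Group main effect, baseline left out | 99% | 87% | 59% |
| Week-12 ANCOVA, same data | 98% | 96% | 94% |

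**Mechanism markers.** The document gives no effect or SD for these, so only the variance ratios apply. Thirty women per arm with ANCOVA are worth 30/0.91 ≈ 33 to 30/0.51 ≈ 59 per arm against a post-score analysis, and 30/0.85 ≈ 35 to 30/0.65 ≈ 46 against change.

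**If the SD of 7 is read as the post-score SD instead,** ANCOVA power is 92.8%, 96.5% and 99.5% at the three correlations. Post-score power is 90.4% throughout, and change-score power is 78.8%, 90.4% and 98.8%. The ordering holds.

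**The case against.** The strongest reply is that section 2.8 does not discard baseline for KI. The main scales go to repeated-measures ANOVA, where baseline may be a visit. The plural may also cover hot flashes, MENQOL, HAMD and HAMA. Section 2.3.4 sizes the trial on change, which itself uses baseline. This stands. A reader might infer that the plan ignores baseline altogether; for KI the document does not establish that. Nor does it clearly assign KI a single-visit post-score comparison, so the 71.5% at ρ = 0.7 should not be read as the trial's power.

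A reader might also infer that chance imbalance at baseline biases the result. It does not. Under randomisation an unadjusted comparison is unbiased, and its standard error already includes chance imbalance, whose SD is √(2/30) ≈ 0.26 outcome SDs. A change-score or group-by-time analysis also takes baseline into account.

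It can further be said that covariates are a matter for the analysis plan, and that no normality pre-test is stated. The second part is fair: no rule for deciding non-normality is given, and no harm from switching tests has been quantified. The first part stands only in part. The article names its between-group methods, and an analysis plan that followed the text would run them unadjusted.

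Finally, the gain depends on ρ. At ρ = 0.3 ANCOVA improves little on a post score (98.2% against 97.1%), and a main effect averaged over post-baseline visits does as well as week-12 ANCOVA.

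**Conclusion.** The concern holds as one of efficiency. Section 2.8 names no baseline covariate, and adding one would use data already being collected.

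- **Mechanism markers, and any scale left outside the repeated-measures analysis:** this is the clearest loss. ANCOVA variance is 0.51 to 0.91 of a post-score analysis and 0.65 to 0.85 of a change-score analysis.
- **KI:** the loss is about 2 to 6 power points if the group-by-time term is tested with baseline as a visit. It is larger at moderate to high correlation if the group main effect is tested (94% falling to 43% with baseline included). ANCOVA stays at about 98% to 94%.

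These figures rest on an assumed ρ of 0.3 to 0.7, equal variances, and, for the repeated-measures results, compound symmetry and an assumed build-up of effect over visits. No bias or type I error inflation is shown.

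**What to change.** State in section 2.8, or in the analysis plan before unblinding, that each continuous outcome is analysed with its own baseline value as a covariate:

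- ANCOVA for outcomes with one post-baseline visit, that is, the mechanism markers at week 12.
- A mixed model for KI, hot flashes, MENQOL, HAMD and HAMA, with baseline as covariate, terms for group, visit and group by visit, and the group contrast at week 12 as the stated test.
- Mann-Whitney tests kept as sensitivity analyses, not as a replacement chosen by distribution.

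A centre term and pre-stated log transforms for skewed markers are optional; the point does not depend on them.

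The cost is wording. No new data, visits or participants are needed, and section 2.10 reports only nine women enrolled by 1 June 2022.

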### 2.5 Outcomes

#### 2.5.1 Primary outcome

The primary outcome of the study is the modified Kupperman Index (KI), which will be measured at baseline and 4, 8, 12, 16 weeks after randomization. The total score of KI is 63. It includes 13 items related to peri-menopausal syndrome, and the severity score of each item ranges from 0 to 3. There were different basic score in each item: hot flashes and sweating = 4; Paresthesia, sleep disorders, nervousness, sexual complaints, urinary tract infection = 2; the other items = 1. Item score = basic score × severity score. Classification standard of disease condition: mild: symptom score <13; moderate: symptom score 14–26; severe: symptom score >27 points.

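### Unless missing values are imputed first, the repeated-measures ANOVA named for the main outcome scales would drop every woman who misses a KI visit, and so would not deliver the promised ITT analysis

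*Protocol article*

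**What the plan says.** Section 2.8 of the protocol article fixes three things in one paragraph:

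- the analysis principle: "All of the analyses will be performed on intention-to-treat (ITT) principle";
- the software: "All data will be statistically analyzed using SPSS 20.0 software";
- the method for the main scales: "The main outcome scales at different time points will be analyzed by repeated measurement analysis of variance (ANOVA").

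Section 2.5.1 names the modified KI as the primary outcome, "which will be measured at baseline and 4, 8, 12, 16 weeks after randomization". That makes five time points, four of them after baseline. Treatment lasts 12 weeks, so Week 16 falls in the off-treatment follow-up (section 2.1 and Table 1).

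The article states no imputation, no mixed model and no other rule for a missed visit. Table 1 has a row for the reasons for drop-out or withdrawal, so loss is foreseen. No rate is given, and section 2.3.4 states no allowance for loss.

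**The concern.** Classical repeated-measures ANOVA treats each woman's series as one multivariate record. The SPSS procedure for it (GLM Repeated Measures) deletes listwise, so one missing value removes the whole record. A woman with KI at Weeks 0, 4, 8 and 12 who misses only Week 16 would contribute nothing, although her treatment period is fully observed.

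Two things are at stake. The first is the population: the method as named does not by itself analyse everyone randomised, which section 2.8 promises. The second is validity. A complete-case contrast is unbiased if values are missing completely at random, or if missingness depends only on arm. It can be biased if women whose KI has worsened, or has improved little, are more likely to miss later visits. Lost power comes on top of this.

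**Working it through.** **Inputs from the documents.** Section 2.3.4 assumes mean KI changes in "the intervention group and the control group were 9 ± 7 and 3 ± 7", so the difference is 9 − 3 = 6 with SD 7 and d = 6/7 = 0.857. The error rates are given "with α equal to 0.05 (two-sided) and β equal to 0.01". The size is stated as: "We determined a sample size of 30 women for each group". Allocation is 1:1 (section 2.2). There are four post-baseline KI visits (section 2.5.1).

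**Inputs assumed.** No missingness rate is given. I use m = 2%, 5% and 10% per post-baseline visit and take baseline as complete.

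**The plan's own figure.** A two-sided test at 0.05 with β = 0.01, difference 6 and SD 7 needs 51 per group, so 30 is not reproduced. With β = 0.10 the requirement is 29 (normal) or 30 (t-based). That mismatch is a separate matter. Here the reference is the power that 30 per arm actually gives: noncentrality 6 / (7 × √(2/30)) = 3.32 on 58 degrees of freedom, power 0.904.

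**Step 1: complete cases.** If all four post-baseline visits enter the model and misses are independent, the complete fraction is (1 − m)^4:

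- 0.98^4 = 0.922
- 0.95^4 = 0.815
- 0.90^4 = 0.656

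**Step 2: the fair comparison.** Comparing with no missing data at all would overstate the fault of the ANOVA, because a Week 12 value that was never collected is lost to any method. The relevant comparator is the women observed at Week 12. Under independent misses that fraction is 1 − m. Under monotone dropout at the same per-visit rate it is (1 − m)^3, since Week 12 is the third post-baseline visit. The complete fraction stays (1 − m)^4 in both patterns.

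**Step 3: power** (two-sample t-test, noncentral t, n = 30 × fraction):

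| m per visit | Complete cases: n per arm, power | Week 12 observed, independent: n per arm, power | Week 12 observed, monotone: n per arm, power |
|---|---|---|---|
| 2% | 27.7, 0.88 | 29.4, 0.90 | 28.2, 0.89 |
| 5% | 24.4, 0.835 | 28.5, 0.89 | 25.7, 0.85 |
| 10% | 19.7, 0.745 | 27.0, 0.87 | 21.9, 0.79 |

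At 5% the loss due to listwise deletion is about 0.02 (monotone: 0.854 − 0.835) to 0.05 (independent: 0.889 − 0.835). At 10% it is about 0.05 (0.791 − 0.745) to 0.13 (0.871 − 0.745). At 2% it is 0.02 or less. These are t-test powers for a single contrast, used as a yardstick; they are not powers of the repeated-measures ANOVA.

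**Step 4: bias, illustration only.** A simulation used true mean changes of 3, 6, 9, 9 against 1, 2, 3, 3 at the four visits, SD 7 and correlation 0.5. Each woman had a 30% chance of leaving after any of the first three visits at which her KI was worse than baseline. Of these inputs, only the 9, 3 and SD 7 come from the document. On average 83% against 71% completed, and the complete-case Week 12 difference was 5.3 against a true 6.0. This shows that bias can arise; it does not predict its size or direction in this trial.

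**The case against.** The strongest reply is that the article never describes a complete-case analysis. It does not name the SPSS GLM procedure, does not say which KI visits enter the model, and does not rule out imputation. Intention-to-treat, imputation and repeated-measures ANOVA together would be coherent and would satisfy section 2.8. A missing-data rule is also commonly left to a full protocol or analysis plan, and neither is shown.

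Much of this stands. A reader might infer that the primary analysis is a complete-case analysis as a matter of fact. The document does not support that: it follows only if visits are missed and nothing is imputed first. What remains is narrower. The article fixes a principle and a method side by side, and the method as named does not by itself deliver the principle. An unseen plan could repair this, but the stated text would still need the repair.

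A reader might also infer that the ANOVA costs the whole fall from 0.90 to 0.835 or 0.745. It does not, because part of that loss follows from Week 12 values that no method can recover. If Week 16 is left out of the model, the complete fraction rises to (1 − m)^3, and under monotone dropout it equals the fraction observed at Week 12.

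Finally, nothing in the document shows that missed visits will depend on symptoms. The bias is a possibility, not an expectation that the text establishes. Exclusion criterion 7 in section 2.3.3, on women who withdraw or are not treated as required, sits awkwardly with intention-to-treat, but it is placed as an eligibility criterion and does not define an analysis set.

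**Conclusion.** The point holds in conditional form. Section 2.8 promises intention-to-treat for every analysis, but the method it names for the main outcome scales would exclude any woman with a missed KI visit in the model unless values are imputed first, and no imputation is stated.

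The size cannot be fixed from the document. Over the assumed range of 2% to 10% missed per visit, 92% to 66% of women would be complete. The power lost to listwise deletion itself runs from under 0.01 (2%, monotone) to about 0.13 (10%, independent). Bias is possible if missed visits depend on earlier KI.

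The conclusion assumes that the main outcome scales include KI, that the classical procedure is used, and that all scheduled visits enter one model. It is worth correcting before analysis, because a better method exists in the same software. It is not evidence that the trial's result will be invalid.

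**What to change.** In section 2.8, replace the repeated-measures ANOVA for KI with a likelihood-based mixed model for repeated measures (SPSS MIXED, REML):

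- use all observed post-baseline KI values, with women analysed as randomised;
- include treatment, visit, treatment-by-visit and baseline KI;
- report the treatment contrast with its 95% CI at one pre-named visit, for example Week 12, the end of treatment.

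This model still omits randomised women with no post-baseline KI, so it is not strictly intention-to-treat alone. Add a sensitivity analysis, for example multiple imputation, that includes them. If the ANOVA is kept, the minimum repair is to state the imputation carried out before it.

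The cost is revised wording and a little more analysis work, with no new visits, data or software. The model relies on a missing-at-random assumption, which is weaker than missing completely at random but cannot be verified from the data. The article reports nine women enrolled by 1 June 2022, so at that date the change could be made well before analysis.
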